## 5. Covariates

Information regarding Socio-demographic background, including sex, age, and education; diagnosed diseases (cardiovascular diseases) will be collected in addition to aforementioned outcomes through self-reported by the participants during the clinical interview in this study and controlled as a covariate in order to explore their potential modifying effects on the primary outcome (cognitive function) in MCI, as evidence reported aforementioned variables as a risk factor for progression from MCI to Alzheimer-type dementia [73,74,75].

### 5.1. Strategies to Promote Participant Retention and Complete Follow-Up

This clinical trial will not provide incentives to increase the retention of participants. Participants will be given telephone calls in case they have doubts regarding the intervention program and its contents. The neurologist in charge of evaluation for the diagnosis of patients with MCI will keep an up-to-date record of the participants’ contact information to prevent data loss during the follow-up period. Participants who decide to withdraw from the study will no longer complete follow-up assessments [76].

### 5.2. Data Management and Confidentiality

The data collected from each participant will be directly stored in electronic forms when participants directly enter the survey or by the recruiters or the outcome evaluators during the trial. After completion, these electronic forms will be submitted online through a safe platform to be automatically downloaded to a unique and encrypted database. No copies of the data will be kept on the electronic devices used in the study (e.g., smartphones, tablets, and personal computers) [76]. Data will be stored in a centralized database [76]. Tin order to protect the confidentiality of participants, other measures will be taken. Once data are registered, the identification of each patient will be eliminated from the database and will be replaced with an ID code. This will make it possible to work with anonymized data, thus protecting the participants’ confidentiality.

## 6. Analysis

Descriptive analyses of relevant variables will be conducted for the total sample and for each group separately in order to assess the balance between the intervention group and the control group after randomization, thus, for categorical variables, the percentage and frequency will be presented for each intervention group, and for continuous variables, means and standard deviations for each intervention group, along with the mean difference between the groups, 95% CI, and *p* value will be presented. In order to determine if there are significant differences in pre and post-evaluation between groups, a mixed design analysis of the variance model with repeated measures (ANOVA) will be performed. One factor, between-subject factor, would consider a “group” (composed of older MCI in the YBM intervention group and older MCI in the active control group with PSE), and the other factor, repeated measures or within subjects’ factor, would be considered as “time” (composed by “pre”, “post”, & “follow up” measures) for primary and secondary outcomes.

In order to report the strength of the YBM intervention, the effect size will be calculated as well, level of significance will be set at *p* < 0.05 with 95% CI, Therefore, based on the repeated measure Anova, effect size calculation would be performed using the standardized mean difference (SMD), Cohen’s d [77]. According to the main outcomes of the study and the condition of the intervention program, since educational level, age and sex are considered as potential confounders o covariates, so they will be controlled at baseline in the Ancova model, and it will enter to model as factor or covariance using the continuous measure. Hence, effect size calculation would be performed using Partial Eta^2^. Moreover, subgroup analyses will be performed to test the possible mediator as well. All the analyses will be based on the intention-to-treat principle, accounting for loss-to-follow-ups, and will be performed using Stata, version 17.0.

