### 2.6. Sample Size

The sample size is estimated based on changing the primary outcome (MoCA) according to the MCID/MCIC (Minimal Clinically Important Difference or Change), which has been established in a study performed by Wong et al. [60]. This Study suggested that a change of 2.0 can be considered as a reasonable minimum, clinically important difference for the main outcome variable (MoCA). Therefore, based on the previous study [32] examining mindfulness’s effect on the cognitive function of seniors with MCI, we estimated the effect size to be 0.5. Hence, we required 18 participants for each arm to have a power of 80% to detect statistical significance at a 5% level which was determined based on an analysis performed in the data of Wong et al. [32] using the Stata 17. Considering potentially a drop-out rate of 20%, 22 participants will be required to be allocated to each group. Therefore, the targeted total sample size will be 44 in order to sustain enough power in the present study.

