### 3.2. Criteria for Stopping or Modifying Allocated Interventions

The neurologist who is in contact with patients for their treatment will be informed If patients allocated to the intervention or to the comparator present worsening of their physical or cognitive function at some point in the trial. Interventions will likewise be interrupted if a patient requests to withdraw from the study. Accordingly, this information will be informed to the affected participant and the Scientific Ethics Committee of the Clinical Hospital of the Universidad de Chile.

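### The repeated-measures ANOVA named in section 6 does not deliver the intention-to-treat analysis accounting for losses that the same section promises

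*Protocol article*

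**What the plan says.** Section 6 (Analysis) of the protocol article fixes the method for the group comparison: "a mixed design analysis of the variance model with repeated measures (ANOVA) will be performed". Group is the between-subject factor. Time is the within-subject factor, "composed by “pre”, “post”, & “follow up” measures) for primary and secondary outcomes". Section 4 and Table 1 give four MoCA assessments: baseline, post-test, 3 months and 6 months.

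The section adds an adjusted model for education, age and sex: "they will be controlled at baseline in the Ancova model". It closes with a promise: "All the analyses will be based on the intention-to-treat principle, accounting for loss-to-follow-ups". Neither the ANOVA nor the ANCOVA, as described, is a means of keeping that promise.

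Section 2.6 expects losses: "Considering potentially a drop-out rate of 20%, 22 participants will be required to be allocated to each group". Section 5.1 states: "Participants who decide to withdraw from the study will no longer complete follow-up assessments". Section 3.2 states: "Interventions will likewise be interrupted if a patient requests to withdraw from the study". Neither section says what happens to the assessments of someone who stops the sessions but does not withdraw from the study.

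**The concern.** A classical repeated-measures ANOVA is built for complete data. A participant with a valid post-test MoCA but no 6-month MoCA is dropped entirely. That is not an analysis of everyone randomised, and it does not account for losses. With 44 participants, each discarded post-test is costly.

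The alternative is to fit the ANOVA to long-format data, so that only the missing rows drop out. This keeps the observed values. It still does not protect the group comparison when leaving depends on earlier scores and the dependence or the rate differs by arm. Unequal losses are possible here: section 3.1 gives one arm a weekly one-hour programme by video and the other a weekly text message.

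At stake is the primary comparison on MoCA, which can be shifted by the choice of model in a way that the intention-to-treat statement tells the reader not to expect.

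**Working it through.** **1. The plan's own drop-out figure.** Inputs from section 2.6: 18 per arm, 20% drop-out, 22 per arm, 44 in total. I take the 18 as stated.
- 18 × 1.2 = 21.6, rounded up to 22: this reproduces the plan's figure. (Dividing instead, 18 / 0.8 = 22.5, gives 23.)
- Expected completers: 22 × 0.8 = 17.6 per arm, or 35.2 of 44.
- Participants with at least one missing visit: 44 × 0.20 = 8.8, about 9 of 44.

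**2. Bias when drop-out depends on the last observed score.** All inputs here are assumptions, not figures from the document: SD 1 at each of four visits, equal correlation 0.6, a true difference of 0.5 SD at every visit after baseline, and 200,000 simulated participants per arm. The chance of leaving before visit t, among those still present, is logit P = a + b × (previous score). The intercept a is set to reach the stated loss by 6 months. Three estimates of the difference in change from baseline are compared:
- complete case: participants with all four visits;
- available rows: least squares with participant effects and visit effects by arm;
- likelihood: multivariate normal fit to all observed values, baseline included in the outcome vector.

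Results at 6 months (true value 0.50):

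| Drop-out | Complete case | Available rows | Likelihood |
|---|---|---|---|
| Random, 20% / 20% | 0.50 | 0.50 | 0.50 |
| Low scorers leave, alike in both arms, 20% / 20% | 0.50 | 0.50 | 0.50 |
| Low scorers leave in YBM only, 20% / 20% | 0.46 | 0.44 | 0.50 |
| Low scorers leave, YBM 30% / control 10% | 0.46 | 0.44 | 0.50 |
| Low scorers leave in YBM, high scorers in control, 20% / 20% | 0.44 | 0.40 | 0.50 |

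The largest errors are 0.06 SD (complete case) and 0.10 SD (available rows). The likelihood estimate stayed within 0.005 SD. In these scenarios every error is an understatement.

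**3. Does the direction hold under other mechanisms?** Assumed: true difference 2.0 points, SD 4, all drop-out after the post-test, YBM 30% and control 10%, slope −1 on the standardised driver of drop-out. The SD of 4 is 2.0 / 0.5; it matches section 2.6 only if its effect size of 0.5 is a standardised mean difference. Complete-case difference in change, for correlations 0.4 / 0.6 / 0.7:

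| Drop-out more likely with | Post-test | 6 months |
|---|---|---|
| Decline from pre to post | 2.70 / 2.58 / 2.49 | 2.37 / 2.28 / 2.26 |
| Low post-test score | 2.39 / 2.26 / 2.18 | 2.00 / 1.99 / 1.99 |
| Low baseline score | 1.63 / 1.73 / 1.78 | 1.62 / 1.74 / 1.79 |

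The errors run from 2.70 − 2.0 = +0.70 (35% of 2.0) to 1.62 − 2.0 = −0.38 (19%). With equal 20% losses driven by decline there was no bias. The available-row ANOVA was unbiased when decline drove drop-out, but gave 1.78 to 1.91 at 6 months when the post-test score did. A likelihood-type estimate gave 2.00 to 2.02 at 6 months under drop-out on decline.

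**The case against.** **Missing detail or a poor choice?** An article may leave its missing-data method to the full protocol or the SAP, and its absence here is no finding. That stands. The point is narrower: the article has already named a model, and the model named does not do what the last sentence of the section promises.

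**Complete cases.** A reader might infer that complete cases will be used and that the intention-to-treat analysis will not be done. The document does not say so. It states the opposite intention and names Stata 17, whose ANOVA on long-format data drops missing rows rather than whole participants. This answers the loss of observed post-tests, but not the bias shown for available rows.

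**Direction of bias.** A reader might infer that benefit will be overstated because YBM is the more demanding arm. The document does not support this. The sign changes with the mechanism, and the 30% / 10% split is assumed; the only rate given is 20%. Also, the second set of scenarios places all losses after the post-test, when the weekly sessions are over. Someone who leaves during the eight weeks has no post-test, and no model recovers it.

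**Sections 3.2 and 5.1.** A reader might infer that these make losses informative. Section 3.2 has the neurologist informed of worsening; it does not say that worsening ends assessment. Section 5.1 concerns withdrawal from the study, where assessments ordinarily end, and it provides for up-to-date contact records to prevent data loss. What remains is that neither section separates stopping the sessions from leaving the study.

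**The likelihood results.** These are close to the truth partly by construction, since the simulated drop-out depends only on observed scores. That is why a sensitivity analysis is still needed.

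**Conclusion.** The point holds as an inconsistency between the named model and the stated analysis principle. In its usual form the ANOVA omits about 9 of 44 randomised participants at the plan's own drop-out rate, including any post-tests they gave. In available-row form it keeps them but can still be biased.

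That bias is conditional. It needs drop-out that depends on scores and differs by arm. Under the assumed mechanisms the 6-month error reached 0.06 SD for complete cases and 0.10 SD for available rows in the first set. In the second set, complete-case errors over both visits ran from −0.38 to +0.70 points around a true 2.0. It is about zero when losses are random or alike in both arms. None of these mechanisms, correlations or SDs comes from the document, so they show what is possible and do not forecast this trial. A better model is available in the software already planned, so the change is worth making.

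**What to change.** - **Section 6:** replace the repeated-measures ANOVA by a likelihood-based linear mixed model for repeated measures, with group, visit and group-by-visit, fitted by REML with small-sample degrees of freedom. Keep baseline MoCA in the outcome vector, or handle it in another way that lets every randomised participant contribute. Restricting the model to those with a post-baseline value would again fall short of intention to treat. Those with a baseline value only add little information on change, and the report should give their number by arm.
- **Section 6:** add one sensitivity analysis for informative drop-out, in which values after drop-out are allowed to differ from what the observed scores predict.
- **Section 5.1:** state that participants who only stop the sessions are still invited to the scheduled assessments, and that assessments end only when a participant declines further data collection. Word section 3.2 so that it agrees.

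The cost is slightly more analysis work in Stata 17, a few sentences of text, and a few more follow-up calls. The sample size and the visit schedule do not change.

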Specific Objectives:(1)To compare the change in cognitive function scores between older adults with MCI receiving a YBM intervention versus those receiving a PES intervention.(2)To compare the change in physical function scores between older adults with MCI receiving a YBM intervention versus those receiving a PES intervention.(3)To compare the change in well-being scores between older adults with MCI receiving a YBM intervention versus those receiving a PES intervention.(4)To compare the change in anxiety and depression scores between older adults with MCI receiving a YBM intervention versus those receiving a PES intervention.(5)To assess the correlation between cognitive function and physical function in older adults with MCI, controlling for psychological variables (depression, anxiety, well-being), and group (YBM intervention or participating in PES)

**Hypothesis 1.** *Older adults with MCI in the YBM intervention will have a different change in their cognitive function—as measured through MoCA assessment, before and after the intervention—than those in the PES intervention (with the same measures, before and after)*.

**Hypothesis 1.1.** *Older adults with MCI in the YBM intervention will have a different change in their physical function—as measured through the Barthel Index (BI) and The Lawton Instrumental Activities of Daily Living Scale (IADL) before and after the intervention—than those in the PES intervention (with same measures, before and after)*.

**Hypothesis 1.2.** *Older adults with MCI in the YBM intervention will have a different change in their well-being—as measured through the Pemberton happiness index, before and after the intervention—than those in the PES intervention (with the same measures, before and after)*.

**Hypothesis 1.3.** *Older adults with MCI in the YBM intervention will have will have lower anxiety and depression levels—as measured through the Geriatric Anxiety Inventory (GAI) and the Geriatric Depression Scale (GDS-5), before and after the intervention—than those in the PES intervention (with same measures, before and after)*.

**Hypothesis 2.** *Cognitive function will have an effect on physical function in older people with MCI, mediated by psychological factors (depression, anxiety, and well-being)*.

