## 4. Outcomes

Blind evaluators to randomization will assess all participants using the telephone-based survey before random assignment (Pre-test), the week following the last session of the intervention (post-test), and then after 3- and 6-months follow-up. It is noteworthy to mention that only the Montreal Cognitive Assessment outcome would be measured via live video call at baseline and post-intervention, 3- and 6-months follow-up.

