### 4.1. Primary Outcomes

(1) Cognitive Function will be measured using a Spanish version of the Montreal Cognitive Assessment (MoCAS1-2) [62] is a short, easy-to-use, and useful test for diagnosing MCI and mild dementia. The test is valid in Chile, each of which has its own evaluation standard. The cut-off points for MCI and mild dementia are <21 and <20, respectively, with sensitivity and specificity rates of 75% and 82% for MCI and 90% and 86% for mild dementia.

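### Section 6 offers two models for MoCA without naming the primary test or visit, and its ANCOVA covariates omit baseline MoCA

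*Protocol article*

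**What the plan says.** All references are to the protocol article.

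- **Hypothesis (section 1).** "Older adults with MCI in the YBM intervention will have a different change in their cognitive function", "as measured through MoCA assessment, before and after the intervention", compared with the PES arm.
- **Primary outcome (section 4.1).** "Cognitive Function will be measured using a Spanish version of the Montreal Cognitive Assessment".
- **Timing (section 4).** "only the Montreal Cognitive Assessment outcome would be measured via live video call at baseline and post-intervention, 3- and 6-months follow-up". Table 1 likewise shows one MoCA before allocation and three after treatment.
- **First model (section 6).** To compare the arms on their pre and post evaluations, "a mixed design analysis of the variance model with repeated measures (ANOVA) will be performed". Group is the between-subject factor. Time is the within-subject factor, with pre, post and follow-up levels. Cohen's d is the effect measure attached to it.
- **Second model (section 6).** "since educational level, age and sex are considered as potential confounders o covariates, so they will be controlled at baseline in the Ancova model". For this model, "effect size calculation would be performed using Partial Eta^2".
- **Covariates (section 5).** Besides sex, age and education, "diagnosed diseases (cardiovascular diseases) will be collected in addition to aforementioned outcomes", and the whole set is described as controlled for. Section 6 does not mention cardiovascular disease.
- **Decision rule (section 6).** A 5% significance level, with no statement of which model, term or visit decides the primary question.
- **Design inputs (section 2.6).** A 2.0-point MCID on MoCA, an effect size of 0.5, and 18 completers per arm (22 allocated).

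**The concern.** Three things do not line up.

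1. The hypothesis is a pre-to-post comparison, but the time factor also holds the follow-up visits. The overall group-by-time test therefore answers a wider question.
2. The ANCOVA names its covariates and leaves out baseline MoCA. That score is normally the best single predictor of later MoCA, and it is already measured in everyone.
3. Two models stand side by side, each with its own standardised effect measure, and neither is marked as primary.

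At stake are precision in a trial planned on 18 completers per arm, and a clear statement of which result would count as evidence for Hypothesis 1. The design rests on a 2.0-point MCID, yet the two effect measures named are not in MoCA points and the article gives no SD with which to convert them.

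**Working it through.** **Inputs.** From the article: 18 completers per arm, effect size 0.5, two-sided 5%, MoCA at four times. Assumed: pre-post correlation rho of 0.4, 0.6 or 0.7 (none is given); equal SDs and equal correlations across visits; both follow-ups entered as levels of time, so the interaction has 3 df; no variance explained by age, sex or education.

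**The plan's own figure.** The article gives no precision or error rate for these models, only 18 per arm. A plain two-group comparison at d = 0.5 needs 2(1.96 + 0.84)²/0.5² ≈ 63 per arm, so 18 is not reproduced that way. That is a separate matter; 18 is used here only as the number analysed.

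**Step 1: precision.** With outcome variance 1, the variance factors are:
- post-test score without baseline: 1
- pre-post change: 2(1 − rho)
- post-test score adjusted for baseline: 1 − rho²

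Ratios to the baseline-adjusted comparison:

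| rho | Change: 2/(1 + rho) | Post score without baseline: 1/(1 − rho²) |
|---|---|---|
| 0.4 | 2/1.4 = 1.43 | 1/0.84 = 1.19 |
| 0.6 | 2/1.6 = 1.25 | 1/0.64 = 1.56 |
| 0.7 | 2/1.7 = 1.18 | 1/0.51 = 1.96 |

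The middle column applies to the pre-post contrast in the ANOVA. The right column applies only if the ANCOVA is a separate model of the post-test score. Both ratios exceed 1 for every rho between 0 and 1.

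**Step 2: power at 18 per arm.** The omnibus interaction has noncentrality (18/2) × Σ(δ_t − mean δ)²/(1 − rho), with 3 and 102 df. Here δ_t is the arm difference in SD units at each visit. The baseline-adjusted post-test contrast has noncentrality 0.5/√[(1 − rho²) × 2/18] = 1.64, 1.88, 2.10 on 33 df.

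| Arm difference at pre, post, 3 months, 6 months | Σ(δ_t − mean δ)² | Omnibus power at rho 0.4 / 0.6 / 0.7 | Adjusted post-test contrast |
|---|---|---|---|
| Constant: 0, 0.5, 0.5, 0.5 | 0.188 | 25 / 36 / 47% | 36 / 44 / 53% |
| Waning: 0, 0.5, 0.25, 0 | 0.172 | 23 / 34 / 44% | 36 / 44 / 53% |
| Growing: 0, 0.5, 0.6, 0.75 | 0.317 | 41 / 58 / 72% | 36 / 44 / 53% |

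The adjusted contrast is ahead for a constant or waning effect; the omnibus test is ahead for a growing one.

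**Step 3: type I error.** Suppose either the interaction test or a separate post-test ANCOVA without baseline could count as success. Simulation under no effect, with 18 per arm and four visits, gives about 9% to 10%. Two independent 5% tests would give 1 − 0.95² = 9.75%.

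**The case against.** The strongest reply is that baseline MoCA is not ignored: it is the first level of the time factor. The ANCOVA may also be the same repeated-measures model with education, age and sex added. With complete data, covariates that do not vary over time leave the group-by-time test unchanged unless they are crossed with time, so the two models would in effect share one interaction test. This stands. It limits the loss to the 2/(1 + rho) column and removes the inflation in step 3. It does not remove the loss, nor the lack of a named contrast.

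Other points also stand in part:

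- **A valid method.** A mixed ANOVA is legitimate in a randomised trial, and the omnibus test gains when the effect builds up. The case for the adjusted contrast rests on its match to Hypothesis 1 and its precision, not on any invalidity of the ANOVA.
- **Multiplicity.** A reader might infer that success could be claimed from a test at any of the three later visits, with a still larger error rate. The article plans no visit-wise tests, so it does not support that. Nor does it say that any significant result will do.
- **Late effects.** A reader might infer that the omnibus test would often be significant with nothing at post-test. That needs a late effect pattern the plan does not state. The hypothesis also does not expressly limit the after measure to the post-test visit.
- **Effect measures.** A reader might infer that results will appear only as Cohen's d and partial eta squared. Section 6 adds these to the tests and does not exclude a difference in points.
- **Covariate lists.** Section 5 partly concerns effect modification, so the mismatch is minor. It does also describe those variables as controlled for, so the two sections should agree.
- **Left to an analysis plan.** Much detail may properly sit there. But this article already fixes two models, a named covariate set and two effect measures, and an analysis plan would have to override them.

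**Conclusion.** The point holds in a limited form. Section 6 sets two models beside each other for a pre/post hypothesis, does not say which model or visit is primary, and names ANCOVA covariates that omit a baseline score already collected.

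Against a baseline-adjusted comparison, variance is 18% to 43% larger for the pre-post contrast at assumed rho of 0.7 to 0.4. It is 19% to 96% larger at rho of 0.4 to 0.7 only if the ANCOVA is a separate post-score model. The direction holds for any rho between 0 and 1; the size depends on a correlation the article does not give, and the MoCA entry limit may lower it. A type I error of about 9% to 10% follows only if the models are separate and either may count as success. The group-by-time test and its 3 df are inferred from the mixed design, since the article does not spell them out. This should be changed, but it does not invalidate the trial.

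**What to change.** In section 6, name one primary test: the YBM minus PES difference in MoCA at post-test, adjusted for baseline MoCA, age, sex and education. Report it in MoCA points with a 95% CI so that it can be read against the 2.0-point MCID.

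- Make the 3- and 6-month differences and the group-by-time test secondary.
- Adjust each secondary outcome for its own baseline value.
- Use the same covariate list in sections 5 and 6. If cardiovascular disease is kept only to explore effect modification, say so in section 5.
- Cohen's d and partial eta squared can stay as supplementary measures.

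The cost is a change of wording and one degree of freedom for the baseline score, with no new data. There is one real trade-off: if the effect grows after post-test, this choice gives up power relative to the omnibus test (36%, 44% and 53% against 41%, 58% and 72% in the growing pattern above).

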Dementia is usually preceded by a phase called mild cognitive impairment (MCI), a stage between the normal cognitive changes caused by aging and early dementia [10]. It encompasses a wide range of cognitive impairments such as memory, executive function, attention, language, or visuospatial skills [11]. Ample evidence has emerged that MCI has become equally prevalent among this segment of the population. A 2016–2017 National Health Survey reported that 10% of adults over 60 years old had suspected MCI, reaching 21% in those over 80 [12]. In the global sample, the prevalence of MCI for ages 60 to 64 years old was 6.7% [13]. However, in adults over 65 years, the prevalence increases to 14.8% and reaches 25.2% in those over 80 [13]. A number of studies have provided evidence that people with MCI are at greater risk of developing Alzheimer’s disease (AD) [14]; 5–15% of people with MCI are diagnosed with AD each year [15].

In addition, the elderly often experience depression and anxiety, which are common in people with MCI [16]. Recent findings indicate that people with MCI have a greater risk of developing the depressive disorder and anxiety disorder [17]. Previous studies show that the proportion of people with MCI who have depressive symptoms ranges between 36% to 63% [18]. Anxiety symptoms are equally frequent, with rates between 10 and 74% [16]. Chileans over 65 diagnosed for the first time with depression presented a greater link with cognitive impairment [19]. Other studies have also shown that depression and anxiety are risk factors for MCI [10,20] and that these conditions often precede the development of AD [21].

The decline in cognitive ability causes difficulty for older people in executing their daily activities [22] and has been associated with declines in functional status, quality of life, and increased dependency as well as mortality [23]. Albala [24] points out that the loss of physiological functioning because of aging reduces the resistance to stressors, leading to the greater vulnerability of older adults and to the development of frailty syndrome [24]. Frailty is strongly associated with cognitive impairment and depression in older Chilean adults [24].

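### Objective 5, the only objective that is not a comparison of randomised arms, omits age, education and sex from its stated control set although the plan itself calls them potential confounders.

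*Protocol article*

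**What the plan says.** Specific Objective 5 (section 1) is "To assess the correlation between cognitive function and physical function in older adults with MCI, controlling for psychological variables (depression, anxiety, well-being), and group", where group means YBM or PES. Hypothesis 2 words the same relation causally, "Cognitive function will have an effect on physical function in older people with MCI", and names depression, anxiety and well-being as mediators.

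Section 6 names the variables regarded as potential confounders and says where they enter: "since educational level, age and sex are considered as potential confounders o covariates, so they will be controlled at baseline in the Ancova model". The sentence concerns the main outcomes and the intervention programme. Section 5 lists sex, age, education and diagnosed cardiovascular disease, to be "controlled as a covariate in order to explore their potential modifying effects on the primary outcome (cognitive function) in MCI". Neither section carries these variables into Objective 5 or Hypothesis 2. The only analysis text that could serve Hypothesis 2 is "subgroup analyses will be performed to test the possible mediator as well", which names no model and no covariates.

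**The concern.** Objectives 1 to 4 compare randomised arms, so age, education and sex cannot confound them on average; adjusting there mainly gains precision. Objective 5 relates two measured traits across participants, and being randomised to YBM or PES does nothing to balance age or education between people with high and low MoCA scores. The plan thus uses its named confounders where bias is least likely and leaves them out where it is most likely.

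The article's own background makes the age pathway plausible. On cognition it reports that "in adults over 65 years, the prevalence increases to 14.8% and reaches 25.2% in those over 80"; on physical function, that "the loss of physiological functioning because of aging reduces the resistance to stressors". Older or less educated participants may score lower on both measures, which produces a correlation that controlling for mood, well-being and group need not remove. At stake is the reading of one non-primary objective: a significant result could be taken as a link between cognition and function when part or all of it reflects age and education.

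**Working it through.** **Inputs from the document.** Section 2.6: 18 per arm evaluable (36 in total), 22 per arm recruited (44 in total). Section 6: 5% significance level; two-sided is assumed. Objective 5: k = 4 control variables (three psychological scores and group). The plan gives no figure for Objective 5, so there is none to reproduce.

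**Assumptions.** There is no direct link between cognition and function. Each confounder correlates with both measures at the same absolute value a = 0.2, 0.3 or 0.4, and all effects act in the same direction.

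**Spurious partial correlation r given the stated controls**

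- A: age, education and sex act as one combined confounder, unrelated to the psychological scores: r = a².
- B: age and education are two independent confounders, unrelated to the psychological scores: r = 2a².
- C: as B, but each psychological score also correlates 0.3 with both confounders. Each score then has covariance 0.3a + 0.3a = 0.6a with each measure, and any two scores correlate 2 × 0.3² = 0.18. The three scores explain k₁ = 3(0.6a)² / (1 + 2 × 0.18) = 0.794a² of each measure, so r = (2a² − k₁) / (1 − k₁).

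**Rejection rate (Fisher z).** At n = 44, z = √(44 − 4 − 3) × atanh(r) = 6.083 × atanh(r), and the rate is Φ(z − 1.96) + Φ(−z − 1.96). For example, B at a = 0.4 gives r = 2 × 0.16 = 0.32, z = 6.083 × 0.3316 = 2.017, rate 52%.

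| a | A: r, rate | B: r, rate | C: r, rate |
|---|---|---|---|
| 0.2 | 0.04, 5.7% | 0.08, 7.8% | 0.05, 6.1% |
| 0.3 | 0.09, 8.5% | 0.18, 19.8% | 0.12, 11.0% |
| 0.4 | 0.16, 16.6% | 0.32, 52.3% | 0.22, 27.7% |

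Simulation with the t test agrees within its error. At n = 44 it gives 6.0%, 9.0% and 16% for A (a separate run gave about 5%, 9% and 17%); 7.8%, 20.3% and 54.1% for B; and about 7%, 11% and 28% for C. At n = 36 it gives 5.8%, 7.9% and 13% for A, and 7%, 17% and 43% for B.

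The bias in r does not shrink as n grows, so the false-positive rate rises with n.

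**After adding age, education and sex (k = 7).** The simulated rate returns to about 5% in every scenario. This holds by construction, because no other confounder was simulated.

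**Price in precision.** The partial correlation detectable with 80% power is tanh(2.80 / √(n − k − 3)). At n = 44 it moves from tanh(2.80 / √37) = 0.43 to tanh(2.80 / √34) = 0.45; at n = 36, from 0.48 to 0.50.

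**The case against.** Several counter-arguments have weight.

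- **The upper figures stack assumptions.** Two independent confounders at 0.4 explain 2 × 0.16 = 32% of the variance of each measure (multiple correlation √0.32 = 0.57). If age and education themselves correlate at −0.3, set-up B gives about 6%, 13% and 34% at n = 44. At a = 0.2 every version is close to nominal. This stands, and is why only a range can be given.
- **Eligibility narrows the scores.** Section 2.3 requires MoCA below 21, no dementia and no problems in daily activities. The Barthel Index covers basic activities (section 4.2), so scores are likely to lie near its ceiling. This stands and favours the lower end of the range.
- **IADL overlaps with cognition.** Section 4.2 says every IADL area needs some cognitive as well as physical function. For IADL the risk is therefore an inflated link, not one created from nothing.
- **An objective is not a model, and a correlation through age is still a correlation.** A fuller document might add covariates. But Objective 5 does not leave the set open: it lists one, and the list does not match the plan's own confounders. Hypothesis 2 then reads the relation as an effect. This lowers the weight of the point without removing it.
- **Cardiovascular disease** is also a section 5 covariate. Section 6 does not include it among the potential confounders, so whether to add it is a choice for the authors to state.

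A reader might infer that Hypothesis 2 would be falsely supported through age and education. The calculation does not show that. Hypothesis 2 concerns a mediated path, and when the psychological scores are unrelated to the confounders, a joint-significance mediation test on the same simulated data rejects in only about 1% of trials. Confounded mediation is possible under other assumptions but is not demonstrated here.

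A reader might also call Objective 5 the plan's only non-randomised analysis. That is too strong, because section 5 also explores covariate effects on cognition and section 6 plans subgroup analyses for a mediator. It is the only listed objective that is not an arm comparison.

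**Conclusion.** The point holds in limited form. Objective 5 states a control set that leaves out three variables the plan itself calls potential confounders, in the one objective that randomisation does not protect. The size rests wholly on assumed correlations: from almost nothing at 0.2 to a serious false-positive rate at 0.4 with two independent confounders, with the low end more plausible given the eligibility criteria. No arm comparison, and so not the primary result, is affected. It is a cheap improvement to a non-primary objective.

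**What to change.** Reword Objective 5 so that the correlation is controlled for baseline age, education and sex as well as the psychological variables and group. Carry the same three covariates into the cognition-function model for Hypothesis 2. Report the result with and without them, and describe it as an association rather than an effect. State whether cardiovascular disease is included, and why.

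The cost is a line or two in the objective and analysis text and three degrees of freedom (at n = 44, from 44 − 2 − 4 = 38 to 35). No new data are needed: section 5 already collects all three, and Table 1 schedules demographics at enrolment.
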